### 8.9.4. Final analysis of inpatient hospital readmissions

Analyses of inpatient hospital readmission will be performed using a Bayesian proportional odds model similar to the one used in section 8.3.3, but with ordinal outcome taking values of -1 for non-survivors to 90 days, 0 for survivors who were readmitted within 90 days, and 2 for survivors who were not readmitted within 90 days. We will first assume that the odds ratios of interventions are proportional across all levels of this outcome. Due to the similarity between

readmission and PDHD outcomes, we will use all model priors from the model in 8.3.3 in the analysis of readmissions. From this model, we will estimate the following posterior probabilities:

- Posterior probability of superiority of each active arm over STS with respect to probability of readmission or death to 90 days
- Posterior probability that each active arm is superior to the other active arms with respect to probability of readmission or death to 90 days

When mortality rates are low, the treatment effects estimated above will approximately equal to the effect on readmission prior to death. However, when mortality rates are high this may not be true. We will therefore also estimate the effect of readmission prior to death on survival to 90 days directly using the (frequentist) Fine and Gray subdistribution hazard model. Coefficients in the linear predictor of this model will mimic the form of the linear predictor in the model of 8.3.3 (minus the intercept terms), including terms for each intervention, the interaction, calendar time if necessary, and relevant risk predictors. From this model, we will estimate the following quantities:

- Difference in cumulative incidence functions for readmission at 90 days and their 95% confidence intervals, for each intervention compared to STS
- Difference in cumulative incidence functions for readmission at 90 days and their 95% confidence intervals, for each intervention compared to other active intervention arms.

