## Measures

### Primary outcome

Post-discharge home days at 90 days: Home days will be calculated as days alive and at home, a composite of mortality and morbidity. We included mortality to ensure that competing risk of death will not affect this outcome. The proposed interventions are likely to have a small effect on time to death in these patients.

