### 6.2. Secondary endpoints

The domain-specific secondary outcome measures are:

Functional Status: will be measured at baseline and 90 days, using the PROMIS Physical Function – for Mobility Aid Users-SF. The Patient-Reported Outcomes Measurement Information System (PROMIS™) provides item banks that offer the potential for PRO measurement that is efficient (minimizes item number without compromising reliability) flexible (enables optional use of interchangeable items), and precise (has minimal error in estimate) measurement of

commonly-studied PROs. PROMIS item banks and their short forms provide evidence they are reliable and precise measures of generic symptoms and functional reports comparable to legacy instruments.

Health-related Quality of Life: will be measured at baseline and 90 days, using the Quality of Life Enjoyment and Satisfaction Questionnaire-SF. The Quality of Life Enjoyment and Satisfaction Questionnaire (Q-LES-Q) is a self-report measure designed to enable investigators to easily obtain sensitive measures of the degree of enjoyment and satisfaction experienced by subjects in various areas of daily functioning.

Transition to Hospice: will be assessed via claims data at 90 days to see if members transitioned to hospice care during the course of the study.

Emergent outpatient utilization: will be assessed via claims data at 90 days for a count of urgent outpatient visits for study participants.

Readmissions: will be assessed via claims data at day 7, 30, and 90 for any inpatient admissions after index admission, and whether readmission hospital was the same as index hospital.

Mortality: will be assessed via claims data at 90 days to see if and when the member/participant passes away.

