## Secondary analyses

- To compare each intervention arm to STS, and to each other, with respect to mortality and PDHD among survivors.
- To determine the effects of each intervention arm and STS on secondary endpoints:
  - Functional status as measured by the PROMIS Physical Function—for Mobility Aid Users
  - Health-related Quality of Life (HQL) as measured by the Quality of Life Enjoyment and Satisfaction Questionnaire-SF (QLESQ-SF)
  - Transition to Hospice. Defined as whether the patient transitioned to hospice care.
  - Emergent outpatient care utilization. Defined as the count of urgent outpatient visits (ED visits and urgent visits).
  - Readmission. Defined as subsequent admission after index admission.
  - Mortality. Whether a patient dies during the first 90 days post discharge to home
- To explore potential heterogeneity of treatment effect

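### SAP 8.9.4 reports a pooled three-level odds ratio as superiority on readmission or death; if mortality is unaffected, it understates that effect

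*Combined protocol and SAP*

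**What the plan says.** The secondary endpoint is readmission after the index stay. SAP 8.1 puts it as "Readmission. Defined as subsequent admission after index admission", and 6.2 adds that it "will be assessed via claims data at day 7, 30, and 90 for any inpatient admissions after index admission".

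Section 8.9.4 first analyses a three-level day-90 outcome. Deaths score -1, and the other two levels are "0 for survivors who were readmitted within 90 days, and 2 for survivors who were not readmitted within 90 days". The model is the Bayesian proportional odds model of the primary analysis: "We will first assume that the odds ratios of interventions are proportional across all levels of this outcome". The first reported quantity is "Posterior probability of superiority of each active arm over STS with respect to probability of readmission or death to 90 days", and a matching one compares the active arms with each other.

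The section then adds a caveat: "When mortality rates are low, the treatment effects estimated above will approximately equal to the effect on readmission prior to death". It warns that this may fail when mortality is high, and adds a Fine and Gray model giving differences in the 90-day cumulative incidence of readmission.

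Two other places bear on this. The protocol's Primary outcome paragraph states: "The proposed interventions are likely to have a small effect on time to death in these patients". SAP 8.5 says that a benefit among survivors with no effect on survival breaks proportional odds. For PDHD the SAP responds with a relaxed model (8.5.2, used in 8.9.3) and with simulations under that violation (12.6).

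**The concern.** The three-level scale has two cuts: dead against alive, and dead or readmitted against alive and not readmitted. The named quantity, readmission or death, is the second cut alone. A proportional odds model estimates one effect for both. If an arm prevents readmissions and leaves deaths alone, the death cut has an odds ratio of 1 and pulls the common estimate toward 1.

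That is the situation the protocol expects and 8.5 describes, yet 8.9.4 has neither a relaxed model nor a binary model. The words about assuming proportionality first imply a later step, but none is specified. The caveat in 8.9.4 concerns readmission before death when mortality is high, not unequal effects at the two cuts. Fine and Gray estimates readmission alone.

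At stake is an understated posterior probability, under a label it does not match, for an outcome that appears in the trial's full name.

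**Working it through.** **Inputs.** Table 2 baseline: death 0.133, 90 home days 0.454. The remaining 0.413 is taken by difference, because the printed cells sum to 0.999. The documents give no 90-day readmission rate, so 90 home days stands in for alive and not readmitted; this is an assumption. The effect is the 12.6 setting: deaths unchanged, odds ratio 1.5 among survivors.

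**1. Reproduce the plan's figures.**
- Survivors with 90 days: 0.454/0.867 = 0.524, odds 1.099.
- Times 1.5 gives odds 1.649, probability 0.622. Times 0.867 gives 0.540. Table 6 states 0.54.
- The severe and SNF strata give 0.468 and 0.291, against 0.47 and 0.29.
- For PDHD, the large-sample proportional odds fit has bias -0.223 at a survivor odds ratio of 1.5. Adding the roughly -0.03 to -0.04 that Table 5.1 shows when proportional odds holds gives about -0.26, as in Table 7.1 scenario 9.

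**2. The composite cut.** (0.5397/0.4603) / (0.454/0.546) = 1.1725/0.8315 = 1.41. The death cut is 1.00.

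**3. The three-level odds ratio.** This is the value of exp(θ) maximising the expected log-likelihood under logit P(Y ≤ j) = α_j − θ·arm, with one θ for both cuts.
- Baseline stratum: about 1.31.
- Full stratum mix (11% severe, 37% SNF, adjusted for both, 30% against 17.5% allocation): 1.255 against a composite odds ratio of 1.410. The log ratio is 0.227/0.344 = 0.66.
- When proportional odds holds at 1.5, both equal 1.50.

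**4. Strength of evidence.** Complete patients: 1,281 × 0.975 = 1,249, using the 2.5% loss stated in the November 2023 power section. STS: 0.30 × 1,249 = 375. Favoured arm from Table 7.2 scenario 3: 473 × 1,249/1,500 ≈ 394. Then n₁n₂/N = 375 × 394/769 = 192.1. Pooled proportions p are 0.133, 0.369 and 0.498.
- Three-level information: 192.1 × (1 − Σp³)/3 = 192.1 × 0.824/3 = 52.8. z = ln(1.311) × √52.8 = 0.271 × 7.26 = 1.97.
- Binary information: 192.1 × 0.498 × 0.502 = 48.0. z = ln(1.410) × √48.0 = 0.344 × 6.93 = 2.38.

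With flat priors these correspond to posterior probabilities of about 0.98 and 0.99.

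**5. Dependence on mortality.** Survivor odds ratio 1.5, deaths unchanged, readmission among survivors assumed at 25% to 47.6% (the upper end counts every survivor with fewer than 90 home days as readmitted):

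| Mortality | Three-level log odds ratio as share of composite log odds ratio | Dilution |
|---|---|---|
| 2% | 97-98% | 2-3% |
| 5% | 92-94% | 6-8% |
| 13.3% | 80-84% | 16-20% |
| 31% | 57-64% | 36-43% |

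The last two rows are the SAP's own baseline and SNF mortality at no treatment effect (Table 4).

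**6. Cost of a binary model if proportional odds holds.** Here the matching arm size is Table 5.2 scenario 3: 607 × 1,249/1,500 ≈ 505. At an odds ratio of 1.5 the information is about 58.1 (three-level) and 53.8 (binary). z is 0.405 × √58.1 = 3.09 against 0.405 × √53.8 ≈ 2.97.

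**The case against.** The ordinal approach is a deliberate way to handle death, consistent with the primary endpoint and 8.9.5, and it is a little more precise when proportional odds holds. The quantity reported is a posterior probability of superiority, with no success threshold set for readmission. With mortality unchanged its direction is right. If mortality turns out low, the dilution is trivial. All of this stands. It limits the size of the problem but does not make the label correct at the mortality the SAP plans for.

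Four stronger readings are tempting and are not supported:

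- *That 8.1 and 8.9.4 contradict each other.* The three-level scale does code a patient who is readmitted and then dies only as a death. But 8.9.4 also analyses readmission itself by Fine and Gray, where that patient counts as readmitted. An endpoint definition and a scale for handling death are different things.
- *That the plan contains nothing close to the composite.* Section 8.5.1 dichotomises PDHD at every level, including 90 days, and 8.10.3 collapses values below 90 for the heterogeneity analyses. These are proxies. No specified analysis directly estimates readmission or death with readmission defined from claims.
- *That the result may point the wrong way.* This needs death and readmission to move in opposite directions, with a sizeable fall in deaths (a death odds ratio near 0.67 in a constructed case). That contradicts the protocol's expectation of a small effect on death.
- *That a stated amount of power is lost.* A power figure needs a decision threshold. The 0.991 in 8.9.1 and 8.12 belongs to the primary endpoint.

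**Conclusion.** The point holds as a mislabelled and diluted secondary result. In the setting the protocol itself expects, the three-level odds ratio is not the odds ratio for readmission or death: about 1.31 against 1.41 in the baseline stratum, about 1.26 against 1.41 over the stratum mix, and expected z about 1.97 against 2.38.

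These sizes rest on 90 home days as a proxy for no readmission, Table 2 and stratum rates taken from pre-trial data, exactly unchanged mortality, a survivor odds ratio of 1.5, and large-sample fits that ignore the priors. The proxy counts stays in post-acute facilities as readmissions, hence the range in step 5. Observed mortality matters most: near 2% the issue is negligible, and at the SAP's 13% to 31% it is material.

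**What to change.** In 8.9.4, estimate readmission or death by day 90 with a Bayesian logistic model for that binary outcome, using the same linear predictor and treatment priors as the primary model. An 8.5.2-type model with a separate death effect would also serve. State the intercept prior, because the 92-level Dirichlet prior of 8.3.3 cannot be carried over unchanged to two or three levels.

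Keep the three-level analysis if wanted, label its result a pooled ordinal effect, and say which of the readmission analyses is the main one.

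The cost is SAP wording and one model on data already held. The statistical downside is a small loss of precision if effects really are proportional: z about 2.96 to 2.97, depending on rounding, against 3.09 at an odds ratio of 1.5.

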#### 8.9.5. Final analysis of ordinal outcomes truncated by death

PROMIS and HRQoL are continuous outcomes collected around day 90 after discharge conditional on survival. Similarly, number of emergency visits by day 90 depends on having 90 days of follow up to be comparable between different treatment arms. Thus, to avoid selection bias we will analyze of these 3 outcomes using a similar composite outcome approach used for the primary outcome, wherein death before day 90 will be treated as the worst outcome on an ordinal scale otherwise consisting of the natural values taken by these variables. For PROMIS and HRQoL, which take positive values, deaths will be assigned a value of -1. For number of emergency visits by day 90, which also takes positive values up to the largest number of visits observed in the sample (K visits), deaths will be assigned a value of K+1. We will use a Bayesian proportional odds model to analyze these outcomes, similar to the approach of the primary analysis in 8.3.3. In our models, each unique value taken by these outcomes will receive its own intercept, a way of modeling continuous outcomes that is competitive with linear regression but which allows us to account for death. The linear predictor of our model will otherwise mimic that of the primary analysis in 8.3.3. From these models, we will estimate the following quantities:

- Posterior probability of superiority of each active arm over STS in terms of surviving with better functional outcomes (PROMIS and HRQoL), or fewer emergency visits within 90 days.

- Posterior probability of superiority of each active arm over all other active arms in terms of surviving with better functional outcomes (PROMIS or HRQoL), or fewer emergency visits within 90 days.

In the event that mortality rates are very small, or that the effect of interventions on mortality rates are very small, we will perform a survivors-only analysis of these endpoints, which is likely to be minimally biased under these conditions.

In these cases, we will analyze these endpoints among survivors to 90 days post-discharge. When modeling these endpoints, we will use Bayesian linear (for PROMIS and HRQoL) or generalized linear (number of emergency visits by 90 days) regression with uninformative priors. The linear predictors of these models will mimic that of the primary analysis in 8.3.3. From these models, we will estimate the following quantities:

- Posterior probability of superiority of each active arm over STS in terms better functional outcomes (PROMIS and HRQoL), or fewer emergency visits within 90 days, among survivors.
- Posterior probability of superiority of each active arm over all other active arms in terms of better functional outcomes (PROMIS or HRQoL), or fewer emergency visits within 90 days, among survivors.

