## Randomization Procedure

The study will use web-based randomization to one of the five care models for those individuals who consent to participate in the study. Once a research coordinator determines eligibility, obtains informed consent, and the patient is discharged to home while maintaining eligibility, he or she will enter in key identification information, and the system will then generate a Study ID (numeric identification number) along with assignment to an intervention arm. Randomization will initially be fixed with 30% of patients randomized to STS and the remaining 70% of patients randomized 1:1:1:1 between the four RPM care models. After 250 patients have been randomized and followed for 90 days, the first interim analyses will be conducted and RAR will begin and continue to be updated every three months. During the RAR phase, the randomization to STS will remain fixed to be 30% of patients and the remaining 70% of patients will be randomized to one of the four RPM models preferentially based on the probability that each RPM care model is optimal.

While the research coordinators will see each assigned intervention arm per the randomization process, they will be blinded to overall changes in treatment allocation rates. Other study team members, including Principal Investigators, Co-Investigators, statistical analysts, and database administrators will also be blinded to treatment allocation rates during the course of data collection.

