The parameters  $\theta_1, \theta_2, \theta_3$  are log odds ratios for active interventions and the parameter,  $\delta$ , is an interaction effect between RPM high and enhanced team. We assume that the effects of each intervention are constant across strata and can be explained by a proportional log-odds ratio shift in the home days distribution. Each intervention's treatment effect is made up of components of the parameters, such that the treatment effect for RPM low/standard is equal to  $\theta_1$ , the effect for RPM high/standard is equal to  $\theta_1 + \theta_2$ , the effect for RPM low/enhanced is equal to  $\theta_1 + \theta_3$ , and the effect for RPM high/enhanced is equal to  $\theta_1 + \theta_2 + \theta_3 + \delta$ . We report these treatment effects as odds ratios, where  $OR_1 = \exp(\theta_1)$  is the odds ratio for RPM low/standard,  $OR_2 = \exp(\theta_1 + \theta_2)$  is the odds ratio for RPM high/standard,  $OR_3 = \exp(\theta_1 + \theta_3)$  is the odds ratio for RPM low/enhanced, and  $OR_4 = \exp(\theta_1 + \theta_2 + \theta_3 + \delta)$  is the odds ratio for RPM high/enhanced. The model is parameterized such that an odds ratio greater than 1 indicates that the care model is beneficial compared to STS.

The variables,  $Z_{i1}$  and  $Z_{i2}$ , are indicators of disease strata for patient  $i$ , where  $Z_{i1} = 1$  when a patient has severe illness (spent time on mechanical ventilation or vasopressors while hospitalized) and  $Z_{i1} = 0$  otherwise, and  $Z_{i2} = 1$  if patient  $i$  has been discharged to a SNF and  $Z_{i2} = 0$  if the patients is discharged immediately to home. With the above model, we assume that the underlying distribution of home days is different within each stratum, and that those differences can be explained by a proportional log-odds ratio shift in the home days distribution through the parameters,  $\beta_1$  and  $\beta_2$ .

Finally,  $p$  additional covariates,  $W_{iCOV}$ , are included in the model with parameters,  $\kappa$ .  $W_{COV}$  contain indicator variables for time at randomization, measured in buckets of 3-month intervals. The first time bucket (furthest in past) will be used as the referent in the model.

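### Baseline PROMIS and Q-LES-Q scores enter neither 90-day model in 8.9.5; an adjusted version is worth prespecifying beside the unadjusted one, because the survey normally follows assignment

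*Combined protocol and SAP*

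**What the plan says.** Domain-Specific Appendix (DSA) 6.2, like the protocol's list of secondary outcomes, schedules both instruments twice: "Functional Status: will be measured at baseline and 90 days, using the PROMIS Physical Function", and "Health-related Quality of Life: will be measured at baseline and 90 days, using the Quality of Life Enjoyment and Satisfaction Questionnaire-SF".

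DSA 8.9.5 analyses the 90-day scores in two ways.
- The main approach is a proportional odds model with death as the worst category: "The linear predictor of our model will otherwise mimic that of the primary analysis in 8.3.3".
- If mortality, or the effect on mortality, is very small, a linear model among survivors is fitted: "The linear predictors of these models will mimic that of the primary analysis in 8.3.3".

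The cited 8.3.3 contains the priors. The linear predictor itself is equation (1) in 8.3.2. It has the treatment terms with their interaction, an indicator for severe illness ("spent time on mechanical ventilation or vasopressors while hospitalized"), an indicator for SNF discharge, and further covariates that "contain indicator variables for time at randomization, measured in buckets of 3-month intervals".

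No change-from-baseline analysis is described. The effect-modifier list in 8.10.1 omits both scores. The multiple-imputation model in 8.11.2 takes in all secondary outcomes and all baseline covariates, without naming these scores.

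**The concern.** A patient's own earlier score is usually a strong predictor of the later one. The two strata in equation (1) were chosen because they predicted home days in pre-trial data; nothing in the documents shows that they predict function or quality of life. Omitting the early score leaves intervals wider than they could be on both patient-reported endpoints.

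Precision is already limited. Planned enrolment was cut to 1,281, and response-adaptive randomization can shrink weaker arms. In Table 5.2, scenario 4, arms 1 to 3 average 104, 128 and 124 patients out of 1,500, before any loss to death or survey non-response.

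Imputation does not close the gap. A variable in the imputation model helps fill in missing values but does not adjust the treatment comparison.

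**Working it through.** The documents state no SD, correlation, effect size or power for PROMIS or Q-LES-Q, so there is no planned figure to reproduce. The correlation r, the 0.25 SD effect and the carried fraction f below are assumptions.

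**1. Patients available.**
- Complete patients: 1,281 × (1 − 0.025) ≈ 1,249, using the 2.5% loss reported with the November 2023 power table.
- Initial allocation: 0.30 × 1,249 ≈ 375 on STS and 0.70 × 1,249 / 4 ≈ 219 per active arm.
- Mortality from DSA 12.1 to 12.2: 13.3% at baseline, shifted by odds ratios 0.75 (severe, 11%) and 0.35 (SNF, 37%), gives 0.133, 0.170, 0.305 and 0.369 for neither, severe, SNF and both. Weighted: 0.561 × 0.133 + 0.069 × 0.170 + 0.329 × 0.305 + 0.041 × 0.369 ≈ 0.202.
- Assumed 80% survey return (DSA 7.1 reports over 80% retention in other studies): 375 × 0.798 × 0.8 ≈ 239 on STS and 219 × 0.798 × 0.8 ≈ 140 in one active arm.

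**2. Survivors-only linear model, early score untouched by treatment.** The residual variance factor is 1 − r². Power is for 0.25 SD, two-sided 0.05, 239 versus 140.

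| r | Variance factor | Equivalent patients | Power |
|---|---|---|---|
| not used | 1.00 | 1.00× | 65% |
| 0.3 | 0.91 | 1.10× | 69% |
| 0.5 | 0.75 | 1.33× | 77% |
| 0.7 | 0.51 | 1.96× | 91% |

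**3. Death-composite model, early score untouched by treatment.** These are simulations with about 20% deaths at the bottom of the scale and a 0.25 SD effect in survivors. Entries are effective sample size, adjusted over unadjusted (ratio of squared mean z). The fitted proportional odds models used 375 versus 375; the rank approximation used 375 versus 219. Where several runs were made, their range is given.

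| r | Fitted model, score unrelated to death | Fitted model, score predicts death (log-odds 0.5 per SD) | Rank approximation, both cases |
|---|---|---|---|
| 0.3 | 1.07 | 1.13 | 1.03 to 1.11 |
| 0.5 | 1.20 to 1.24 | 1.24 to 1.37 | 1.10 to 1.22 |
| 0.7 | 1.41 to 1.57 | 1.73 | 1.25 to 1.44 |

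**4. When the survey is taken.** The arm is generated once the coordinator "obtains informed consent, and the patient is discharged to home while maintaining eligibility" (protocol, Randomization Procedure). DSA 5.1 has the intervention in place by the first complete weekday at home. The protocol's timeline allows two weeks at home for the baseline survey, and the Enhanced Team's first contact falls in the week after discharge. The score therefore cannot be assumed to precede treatment.

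**5. What that does to adjustment.** If the early score already carries a fraction f of the 90-day effect, the adjusted linear estimate shrinks by the factor 1 − rf, and relative efficiency is (1 − rf)² / (1 − r²).
- r = 0.5, f = 0.25: 0.875² / 0.75 = 1.02.
- r = 0.5, f = 0.5: 0.75² / 0.75 = 0.75.
- Power at r = 0.5 for f = 0, 0.1, 0.25 and 0.5: 77%, 73%, 66% and 53%, against 65% unadjusted.

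For the composite model (simulated, 375 versus 375):

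| Setting | f = 0 | f = 0.25 | f = 0.5 |
|---|---|---|---|
| r = 0.5, score unrelated to death | 1.24 | 0.95 | 0.69 |
| r = 0.5, score predicts death | 1.37 | 0.93 | 0.57 |
| r = 0.7, score unrelated to death | 1.57 | 1.07 | 0.66 |

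If the effect built up evenly over 90 days, a survey at day 7 to 14 would carry 7/90 = 8% to 14/90 = 16%. A separate composite run at r = 0.5 put the remaining gain in that range at about 1.05 to 1.07, which is small next to simulation noise.

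**The case against.** The strongest case for leaving the models alone is that the score is not a true baseline. It is collected after assignment, in a trial where the treating teams are unblinded. A difference between arms on this survey may be an early treatment effect, and adjusting for it pulls the estimate toward the null. The unadjusted comparison is protected by randomization, and omitting a prognostic covariate does not bias it. Only two secondary endpoints are involved, and no success threshold is attached to them.

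Most of this stands, and it rules out two stronger readings. A reader might infer that the plan throws away a known amount of precision. The documents do not support that: they give no correlation, and the gain depends on how much treatment effect the survey already contains. A reader might also infer that the adjusted model should replace the unadjusted one. Step 5 shows why that is unsafe.

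Missing scores are a further difficulty. Patients who die or are readmitted soon after returning home may have no survey, yet the composite keeps every death, so missingness can depend on the outcome.

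What does not stand is silence. The plan schedules these scores and gives no reason for leaving them out. Where treatment affects neither score, adjustment creates no spurious effect.

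**Conclusion.** The omission is real: neither model in 8.9.5 uses the early PROMIS or Q-LES-Q score. The statement is limited to the analysis models, since the imputation model in 8.11.2 may include the scores.

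If the score is unaffected by treatment, the composite model gains roughly 1.1, 1.2 and 1.4 to 1.7 times the effective sample size at r = 0.3, 0.5 and 0.7. Survivors-only residual variance falls by 9%, 25% and 49%. If the survey already reflects treatment, the gain shrinks: at r = 0.5 it is about gone at f = 0.25 and reversed at f = 0.5. All of this rests on assumed r and f, a 0.25 SD effect and about 20% mortality.

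The point supports an adjusted analysis alongside the unadjusted one, with survey timing handled openly. It does not show that the unadjusted analysis is invalid, and the primary analysis and its type I error are untouched.

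**What to change.** In 8.9.5:
1. Prespecify a baseline-adjusted version of each model, composite and survivors-only, with baseline PROMIS in the PROMIS model and baseline Q-LES-Q in the quality-of-life model.
2. Report it beside the unadjusted model, kept in full and not demoted, and state in advance which one leads.
3. Use the survey date relative to randomization and intervention start, define intervention start for STS, and run a sensitivity analysis comparing surveys completed before and after it. Tabulate survey timing by arm, since timing may itself differ between arms.
4. Correct the cross-reference for the linear predictor from 8.3.3 to 8.3.2.

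In 8.11.2, name both baseline scores in the imputation model. State how a missing baseline is handled for patients who die or are readmitted before the survey, so that adjustment does not drop known deaths from the composite.

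The cost is one covariate in each model for two secondary endpoints, one timing analysis and a few sentences of text. No new assessments are needed, provided the survey and intervention-start dates are recorded. The risk of attenuation remains visible because the unadjusted result is reported alongside.
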